**Fig. 3 Fig3:**
[figure not shown]
Moxibustion apparatus. **a** base, **b** adjustable holder, **c** flexible tube, **d** clamp

### Intervention

Patients in each group will receive moxibustion using the corresponding moxa sticks (group A: moxa stick A; group B: moxa stick B; and group C: moxa stick C) on three standard acupoints (ST35, Ex-LE04, and Ex-LE02) of the affected knee 20 min per session, three sessions per week (ideally every other day) for 2 weeks. For patients with both knees affected, treatments will be provided on the knee with more severe baseline pain. The treatment will be conducted at a room temperature of 22–26 °C. A four-head, floor-type moxibustion apparatus, consisting of a base, an adjustable holder and four flexible tubes with clamps, will be used for the implementation of moxibustion (Fig. 4). The three groups will share the same moxibustion procedure as follows: (1) patients will be kept in a supine position with their knees slightly flexed (a soft, rolled blanket may be placed under the knee joints) to avoid hyperextension; (2) the holder of the moxibustion apparatus will be adjusted to a proper height; each of the three used clamps will be fixed to one end of the moxa stick with at least 6 cm left in the other end (named the burning tip); and the flexible tubes will be adjusted to make each burning tip of the moxa stick 2.5–3 cm above each acupoint; (3) the burning tips of the three moxa sticks will be ignited; (4) patients will be required to feel an intolerable causalgia (approximately 40–43 °C) within 5 min. Once this is attained, the height of the burning tip will be quickly adjusted to allow patients to keep a comfortable moxibustion sensation during the rest of the treatment.

**Fig. 4 Fig4:**
[figure not shown]
SPIRIT Figure

Throughout the trial, the patients will be discouraged from receiving drug therapy for KOA, including acetaminophen, NSAIDs, other analgesics, etc. For any unallowed treatment that has already been used, relevant information should be recorded in the patient’s electronic Case Report Form (eCRF) in detail. Medicine used for other diseases will not be forbidden.

### Outcome measures

The primary outcome will be the change in the score on the pain subscale (pain score) of the WOMAC from baseline to week 2.

The WOMAC is a widely used disease-specific measurement for function of hip and/or knee OA [19]. It consists of 24 items divided into 3 subscales addressing severity of joint pain (5 items), stiffness (2 items) and limitation of physical function (17 items), respectively, in the previous 48 h. In this trial, a validated Chinese WOMAC [20] will be used. Each item of WOMAC will be assessed by a 100 mm visual analogue scale (VAS), with a higher score indicating worse symptom severity. Items will be summed for each subscale, resulting in possible ranges as follows: pain, 0–500 mm; stiffness, 0–200 mm and physical function, 0–1700 mm. A total WOMAC score is a sum of the scores for all three subscales, with 2400 mm being the worst possible total score.

Secondary outcomes include the change in the WOMAC pain score from baseline to week 6; the change from baseline to weeks 2 and 6 in knee pain (measured by a 100 mm VAS with higher score indicating more severe pain), the total WOMAC score, the WOMAC stiffness score, the WOMAC function score, and the patient global assessment (PGA) (measured by a 100 mm VAS with a higher score indicating a patient more greatly affected by KOA); and the responder criteria developed by the Outcome Measures in Rheumatology Arthritis Clinical Trials-Osteoarthritis Research Society International (OMERACT-OARSI) criteria [21]. The OMERACT-OARSI responders are defined as patients with (1) at least 50% improvement and an absolute change of at least 20 points in the WOMAC pain score or WOMAC function score; or (2) at least 20% improvement and an absolute change of at least 10 points in any two of the WOMAC pain score, the WOMAC function score, and the PGA.

The change from baseline in skin temperature for each acupoint (ST35, Ex-LE04, and Ex-LE02) at 5 min, 10 min, and 15 min during moxibustion will be assessed using an UT-325 Contact Type Thermometer (Uni-Trend Technology (China) Limited, Guangdong, China). A total of 30 patients will be randomly selected from patients in the Institute of Acupuncture and Moxibustion CACMS, 10 patients per group. The skin temperature for each acupoint will be measured at 5 min, 10 min, and 15 min during moxibustion, three measures for each acupoint per moxibustion session, totaling six sessions of moxibustion. The skin temperature for each acupoint at each corresponding time point is defined as the mean of total skin temperatures measured at the corresponding time point during each of the six moxibustion sessions. For example, the skin temperature for ST35 at 5 min during moxibustion is the mean of total skin temperatures measured at 5 min during each of the six moxibustion sessions.

Adverse events (AEs) will be appropriately monitored, managed, and documented throughout the trial. According to their potential association with moxibustion, the AEs will be categorized by acupuncturists as treatment-related or non-treatment-related within 24 h of their occurrence. AEs related to moxibustion mainly include symptoms of excessive heat: dryness of eye, mouth, throat, or nose, sore throat, eye itching, runny nose, tearing, swelling, and aching of gum, etc.; skin symptoms: empyrosis, rubefaction, blistering, itching sensations, pigmentation, etc.; or other symptoms: general fatigue, dizziness insomnia, drowsiness, constipation, diarrhea, flatus, etc.

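### The responder rule applies 20- and 10-point absolute thresholds to unrescaled WOMAC sums, so that condition hardly operates for pain and function; the excess of responders is probably small

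*Protocol article*

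**What the plan says.** All the elements stand in the protocol article under Outcome measures.

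- **Scoring of WOMAC.** Each item is a 100 mm visual analogue scale and items are added within each subscale, giving "pain, 0–500 mm; stiffness, 0–200 mm and physical function, 0–1700 mm".
- **Scoring of PGA.** A single scale, "measured by a 100 mm VAS with a higher score indicating a patient more greatly affected by KOA".
- **Responder route 1.** "at least 50% improvement and an absolute change of at least 20 points in the WOMAC pain score or WOMAC function score". PGA plays no part in this route.
- **Responder route 2.** A 20% improvement together with "an absolute change of at least 10 points in any two of the WOMAC pain score, the WOMAC function score, and the PGA".

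The section does not say that pain or function is converted to a 0–100 score before the rule is applied, and it does not tie the word *points* to millimetres or to a standardised score. Under Participants, entry is limited to a total WOMAC above 49 and up to 72 on a 0–96 scale. The responder outcome is secondary, and the abstract places it at weeks 2 and 6.

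**The concern.** Each route joins a relative condition to an absolute one. The absolute part is there so that a large percentage of a small baseline does not count as a response. It can do this only if the threshold is a meaningful share of the scale.

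Here the scales differ in length by a factor of 5 (pain against PGA) and 17 (function against PGA), yet route 2 uses one 10-point threshold for all three and lets any two of them qualify. Route 1 likewise uses one 20-point threshold for pain and function, whose ranges differ by a factor of 3.4 (1700/500).

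At stake is whether the responder proportion reflects the two-part rule that the article sets out, or in effect a percentage rule for pain and function with an absolute check left only on PGA. Two analysts could also derive different responders, one working on the stated sums and the other assuming 0–100 scores.

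**Working it through.** **1. Ranges (Outcome measures).** Pain 5 × 100 = 500 mm; function 17 × 100 = 1700 mm; total 24 × 100 = 2400 mm. The article's own ranges reproduce.

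**2. Thresholds as a share of range.**

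| Score | Range | 20 points | 10 points |
|---|---|---|---|
| Pain | 500 | 20/500 = 4.0% | 10/500 = 2.0% |
| Function | 1700 | 20/1700 = 1.2% | 10/1700 = 0.6% |
| PGA | 100 | not used | 10/100 = 10% |

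**3. When the absolute condition adds anything.** It binds only if the required percentage of baseline is smaller than the absolute threshold, that is, if baseline < absolute/relative.

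- Route 1: 20/0.5 = 40 mm, which is 8.0% of the pain range and 2.4% of the function range.
- Route 2: 10/0.2 = 50 mm, which is 10.0% of the pain range, 2.9% of the function range and 50% of the PGA range.

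On a common 0–100 scale the same limits would be 40% and 50% of range for every score: pain below 200 or 250 mm, function below 680 or 850 mm.

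**4. Direction.** The 0–100 thresholds in raw units are 100 and 50 mm for pain (× 5) and 340 and 170 mm for function (× 17). These exceed 20 and 10 mm. The percentage conditions and the PGA test are the same under both readings. So everyone who responds on the common scale also responds under the rule as written, and the rule as written can only add responders.

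**5. What the entry window does.** 49/96 = 51% and 72/96 = 75% of range. Assume that this share carries over from the 0–96 entry scale to the VAS scores and is equal across subscales. A patient at the floor then gains 0.5 × 51.04 = 25.5 of 100 with a 50% improvement and 0.2 × 51.04 = 10.2 of 100 with a 20% improvement. Both already pass 20 and 10. For such patients the percentage condition decides on either scale.

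**6. Who is still affected.** The window limits only the total, and pain is 5 of 24 items. Take pain at 30%, stiffness at 50% and function at 60% of range: (5 × 0.30 + 2 × 0.50 + 17 × 0.60)/24 = 12.7/24, and 12.7 × 4 = 50.8 of 96, which is eligible.

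- If pain falls from 150 to 75 mm, the patient meets route 1 on pain alone as written (50%, 75 mm). Rescaled, the change is 15 of 100 and route 1 fails. If neither function nor PGA meets its route 2 test, the classification changes.
- If pain falls by 20% (30 mm, or 6 of 100), the pain part of route 2 is met as written and missed when rescaled.

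A low PGA cannot create an excess responder by itself, because its test is the same under both readings. It matters only by making the pain or function test decisive.

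**7. Size.** Simulation under assumptions, 400,000 patients per setting: total uniform over 51–75% of range; pain and PGA scattered around it with SD 5 to 20 of 100, function with one third of that; mean improvement 5 to 20, SD 12 to 15, correlation 0.6. Raw-rule minus rescaled-rule responder rate, in percentage points:

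| Scatter SD | Excess |
|---|---|
| 5 | 0.03 to 0.05 |
| 10 | 0.15 to 0.26 |
| 15 | 0.4 to 0.7 |
| 20 | 0.9 to 1.5 |

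The largest value is 0.4097 against 0.3949. In an arm of 140 that is 140 × 0.0148 ≈ 2 patients.

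**The case against.** The strongest reply is that the defect changes little. Entry starts at about 51% of the total range, so the absolute condition would seldom bind even after rescaling. Function makes up 17 of 24 items and cannot easily depart from the total. The same rule applies in all arms, and no bias in a between-arm comparison has been shown. With p near 0.5, the standard error of the A–B difference in responder proportions is about 0.5 × √(2/140) = 0.06, or 6 percentage points, well above any excess in the table. All of this stands, and it limits the size of the point.

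A second reply is that *points* may mean standardised scores. The Sample size section also speaks of points, with standard deviations of 10 and 12, which would be only 2% and 2.4% of a 0–500 sum. That is a fair reading of the intention. But Outcome measures defines the pain and function scores as sums and applies the thresholds to those scores. A reader who follows the text gets the raw rule. This is a stated rule that misfires, not a detail left to a fuller document.

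A reader might infer more than the documents support:

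- **That the 20-point threshold also falls on PGA.** It does not; only the 10-point threshold is shared with PGA.
- **That responder rates are materially inflated.** Illustrative excesses of 2–3 or 6–7 percentage points need mean baselines of 50 or 40 of 100, below the entry floor of about 51% on the total.
- **That the rates cannot be compared with other trials.** Nothing in the article shows how other trials scale these scores, and the cited criteria are not at hand.

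**Conclusion.** The point holds in limited form. On the scores as the article defines them, the absolute-change condition is almost inoperative for pain and function, while for PGA it is a real hurdle of 10% of range. The direction is certain: compared with a common 0–100 scale, the rule can only add responders.

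The size is likely small, about 0.03 to 1.5 percentage points. The upper end needs pain and PGA to scatter widely around the total (SD 20 of 100). The excess falls on patients whose pain, or less plausibly function, lies well below their total score, more so where a low PGA leaves the pain test to decide. This range rests on the simulation inputs and on carrying the 51–75% window from the 0–96 scale to the VAS; the documents give neither.

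The outcome is secondary. The primary outcome, the change in WOMAC pain at week 2, and the sample size do not use the rule. It is worth correcting because the text gives a rule that does not do what its two parts are built to do, not because trial conclusions are likely to turn on it.

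**What to change.** State under Outcome measures that pain (sum/5) and function (sum/17) are rescaled to 0–100 before the responder thresholds are applied. Equivalently, give the thresholds in mm:

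| Score | Route 1 | Route 2 |
|---|---|---|
| Pain | 100 mm | 50 mm |
| Function | 340 mm | 170 mm |
| PGA | not used | 10 mm (unchanged) |

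This is one sentence in the derivation rules. It needs no new data and no change to the sample size or the primary analysis. The article reports that recruitment is under way, so the sentence should be fixed before unblinding, so that the choice of scale is not made with results in view. The only downside is that responder rates may be marginally lower.

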### Statistical methods

#### Sample size

There are no previous clinical studies comparing different habitats of moxa floss, or are there studies comparing moxa floss with non-moxa floss for the effect of moxibustion. Based on the results of a study investigating moxibustion versus a heat-insulated placebo moxibustion for KOA [22], we assumed a standard deviation of 10 for group C (sham moxibustion), and 12 for groups A and B (moxibustion). The sample size calculation was based on the formula of one-way analysis of variance (ANOVA) with pairwise comparisons, with 80% power, a two-sided significance level of 5% and a 15% dropout rate. We designed this study to detect: (1) a difference of 5 points in the WOMAC pain score for comparison between moxibustion using different habitat moxa floss; that is groups A and B with an allocation ratio of 1:1; and (2) a minimal clinically important difference of 10 points [23, 24] for comparison between moxibustion (group A or B) and sham moxibustion (group C) with an allocation ratio of 2:1. For the first comparison, 140 participants will be needed for groups A and B; for the second comparison, 45 participants will be needed for group C, and 90 for groups A or B. The larger result from the first comparison was then used to determine the final sample size, that is, 140 participants in groups A and B, respectively, and 70 in group C. The total sample size is 350 participants.

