### Participants

This trial plans to recruit 350 participants with moderate to severe KOA from the outpatients of the acupuncture and moxibustion clinics of the four hospitals via poster, website, and WeChat.

Participants will be included if they fulfill the following criteria: (1) aged 50–80 years; (2) diagnosed as primary KOA according to the American College of Rheumatology clinical and radiographic criteria [16] (knee pain; osteophytes; and at least one of the three following conditions: (a) age > 50 years; (b) stiffness < 30 min; (c) crepitus); (3) radiological assessment of KOA rated as grade 2 or 3 on the Kellgren-Lawrence Grading Scale [17] (grade 2: definite osteophytes and possible joint space narrowing on anteroposterior weight-bearing radiograph; grade 3: multiple osteophytes, definite joint space narrowing, sclerosis, and possible bony deformity); and (4) an overall score of > 49 to ≤ 72 on the Western Ontario and McMaster Universities Osteoarthritis Index (WOMAC) (0–96) [18]; that is moderate to severe KOA.

Participants will be excluded with any of the following items: (1) secondary KOA; (2) significant trauma or surgery history in the target knee joint within 1 year, or severe knee joint deformity (varus or valgum with an angle of at least 8 degrees); (3) recent intra-articular injection with glucocorticoids < 3 months previously or hyaluronic acid < 2 weeks previously, or acupuncture or moxibustion treatment within 2 weeks; (4) symptomatic hip OA or patellofemoral arthritis homolateral to the target knee; (5) inflammatory diseases including rheumatoid arthritis; (6) acute meniscus injury or ligamentous injury or rupture of knee joint; (7) knee joint peripheral tumor, tuberculosis or spontaneous osteonecrosis of the knee; (8) taking paracetamol, an anti-inflammatory agent or an analgesic for other diseases; (9) uncontrolled hypertension or diabetes, tumor or serious cardiovascular, cerebral, lung, liver, spleen, kidney, hematopoietic, hemorrhagic or psychiatric disease; (10) scar diathesis or sensory disorder; (11) pregnant or lactating women; (12) refusal to sign informed consent.

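### WOMAC sits on incompatible or unlabelled scales: a 0–500 mm primary score, planning SDs and differences with no stated scale, and a 0–96 entry band

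*Protocol article*

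**What the plan says.** The protocol article treats WOMAC in four places.

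- **Outcome measures, scoring.** "The primary outcome will be the change in the score on the pain subscale (pain score) of the WOMAC from baseline to week 2". "Each item of WOMAC will be assessed by a 100 mm visual analogue scale (VAS"), and items are summed without division, giving "pain, 0–500 mm; stiffness, 0–200 mm and physical function, 0–1700 mm". The total is the sum of all three subscales, "with 2400 mm being the worst possible total score".
- **Outcome measures, responder rule.** An absolute change of at least 20 points is required in pain or function, or of at least 10 points in any two of pain, function and the patient global assessment. The last of these is a single 100 mm VAS.
- **Sample size.** "we assumed a standard deviation of 10 for group C (sham moxibustion), and 12 for groups A and B (moxibustion"). The habitat comparison (A against B) is to detect 5 points in the WOMAC pain score. The comparison with sham uses "a minimal clinically important difference of 10 points". No range or unit accompanies any of these values. The SDs and the 10 points are attributed to outside studies.
- **Participants.** Entry requires an overall score of >49 to ≤72 on the "Universities Osteoarthritis Index (WOMAC) (0–96"), labelled moderate to severe disease.

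No section describes a second version of the instrument or a conversion between these scales.

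**The concern.** The sample size section and the outcome section use the same name, WOMAC pain score, but the planning values look as if they belong to a different scale from the one defined. A reader who combines the two sections would conclude that the trial is sized for a 5 mm habitat difference on a 0–500 mm sum and that 10 mm against sham matters clinically. If the values come from a 0–100 score, both readings are too small by a factor of five. The responder thresholds have the same ambiguity.

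The entry band is a separate inconsistency. The only scoring described cannot be read on 0–96 without a conversion or a second form, and four centres have to apply the criterion.

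**Working it through.** **1. Reproduce the planned size.** Inputs from Sample size: difference 5, SD 12, 80% power, two-sided 5%, 15% dropout, pairwise comparisons among three groups (read as alpha 0.05/3).

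n per arm = 2 × SD² × (z₁₋α/₂ + z₀.₈)² / difference² = 2 × 144 × (2.394 + 0.842)² / 25 = 120.6, so 121.

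Inflated as 121 × 1.15 = 139.15, so 140, which is the stated figure. Dividing by 0.85 instead gives 143. With 119 completers per arm (140 × 0.85) and Tukey critical values, power is 80.4%. The calculation that sets the total is sound on its own inputs.

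**2. Compare the planning values with candidate ranges.**

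| Value | Share of 0–500 | Share of 0–100 |
|---|---|---|
| difference 5 | 1% | 5% |
| difference 10 | 2% | 10% |
| SD 12 | 2.4% | 12% |

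On a 0–20 pain score, 10 points would be half the range. For a sum of five equally variable items, an SD of 12 mm implies an item SD of 12/5 = 2.4 mm if the items are perfectly correlated and 12/√5 = 5.4 mm if they are uncorrelated. That is very tight for patient-reported pain on a 100 mm line.

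**3. Responder rule.** Ten points is 10/500 = 2% of the pain range, 10/1700 = 0.6% of the function range and 10% of the global assessment range. A common threshold makes sense mainly if points are on a 0–100 score, which the protocol never defines.

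**4. Reading A: SDs and differences share one scale, taken as 0–100.** Multiply by 5: differences 25 mm and 50 mm, SD 60 mm. The ratio 25/60 = 5/12 = 0.417 is unchanged, so n is still 121 per arm before dropout and power is still about 80%. What changes is the difference the trial can detect on the score as defined.

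**5. Reading B: 5 mm meant literally on 0–500 mm.** The documents give no SD on that scale, so the SDs below, other than 12, are assumptions. Two-sample comparison, 119 per arm, alpha 0.05/3:

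| SD (mm) | Power for 5 mm |
|---|---|
| 12 | 79% |
| 25 | 19% |
| 30 | 13% |
| 60 | 4% |
| 100 | 2% |

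**6. Entry band.** On 0–96, 49/96 = 51% and 72/96 = 75% of the maximum. Read literally on 0–2400 mm, 49/2400 = 2.0% and 72/2400 = 3.0%, or about 2 to 3 mm per item over 24 items. That does not match the label of moderate to severe. The band plays no part in the power calculation.

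**The case against.** The strongest reply is that power depends only on the ratio of difference to SD, and the protocol gives both together in one calculation. Linear rescaling leaves the ratio, the sample size and the planned ANCOVA unaffected. A reader might infer from the mismatch that the trial has almost no power. The documents do not support that: the low figures under Reading B arise only if the SD is enlarged to suit 0–500 mm while the difference stays at 5. The text uses mm for raw sums and points for thresholds, which makes the literal 5 mm reading the less likely one. This part of the reply stands.

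Three further replies stand in part.

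- The scale of the SDs and of the 10-point difference rests on cited studies that are not at hand, so 0–100 is an inference. Only the poor fit to 0–500 mm can be shown.
- The analysis section applies no 10-point decision rule, so the risk of calling 10 mm important concerns interpretation rather than the test.
- A separate 0–96 form may be used at screening, and staff are trained in participant selection. A reader might infer that baseline severity will drift between sites, but nothing in the documents shows this.

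None of these replies supplies the missing scale or conversion.

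**Conclusion.** This is an inconsistency of scale, not an arithmetic error. As written, the 5-point and 10-point differences cannot sensibly be applied to the 0–500 mm score, nor the entry band to the 0–2400 mm total.

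The size of the effect depends on an unstated fact. If the SDs and differences share a 0–100 scale, 140 per arm and about 80% power stand, and the differences on the primary score are 25 mm and 50 mm, five times the face value. If 5 mm is literal and the SD is 25–100 mm, power for the habitat comparison is about 19%–2%. Loss of power is therefore conditional and is not established.

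The point still needs correcting before results are read, because it affects the meaning of the primary difference, the importance threshold, the responder definition and eligibility.

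**What to change.** 1. Check the scale used in the studies cited for the SDs and for the minimal important difference.
2. State the scale of SD 10 and 12 and of the 5- and 10-point differences. Then either restate them in mm on 0–500 or report the pain score on the planning scale.
3. Put the 10- and 20-point responder thresholds on the same stated scale.
4. Reconcile the 0–96 entry band in Participants with the 0–2400 mm scoring in Outcome measures, for example by stating whether a separate 0–96 form is used at screening. A proportional conversion of the band should not be assumed, because the documents do not show that the two response formats are equivalent.

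The cost is wording in the protocol and analysis plan, with no new data. The total of 350 is unchanged if the planning SDs and differences prove to share one scale. If they do not, the sample size justification has to be redone.
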